#### 1435 *Power Analysis*

1436 The objectives of aim 1 are to 1) explore the predictive relationship between ascending factors of  
1437 interest and pain reduction due to our interventions; 2) test the association between the ascending  
1438 factors and pain reduction. However, because the former is exploratory in nature, we will design our  
1439 study to power for the latter objective. Specifically, we compute the number of patients needed to find  
1440 an association between key baseline parameters (pressure pain threshold, temporal summation (TS), or  
1441 widespread pain) and pain reduction due to verum treatment. With 50 patients per arm, we will be able  
1442 to detect a moderate correlation of 0.4 (supported by literature for pressure pain threshold and TS)  
1443 with approximately 80% power with alpha of 0.05 using Fisher's transformation. Next, to determine if  
1444 the association is stronger in the verum than the sham arm, we will test the interaction between  
1445 treatment and the baseline parameters. Fifty patients per arm will provide 80% power (with alpha of  
1446 0.05) to detect a moderate difference of 0.5 between correlation from the verum arm and that from the  
1447 sham arm. Therefore, we are adequately powered to detect a moderate association between baseline  
1448 parameters and the clinical response in the verum acupuncture arm and a moderate difference in the  
1449 strengths of these associations between the verum and the sham treatment group.

1450 Similar calculation with identical numbers can be found for aim 2 (descending factors). Note prior  
1451 literature supports a moderate association around 0.4 between catastrophizing and pain reduction as  
1452 well as between self-efficacy and pain reduction in patients suffering from chronic low back pain.

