## 9.6 Data Analyses

**Aim 1. Explore the predictive relationship and the association between ascending sensitization measures and clinical response to acupuncture.**

**Planned analysis:** There are two specific goals of the analysis: (1) explore the predictive relationship between key baseline parameters and treatment response (pain reduction) accordingly by arm; and (2) examine the associations between baseline predictors and treatment response by arm. The identified association can help us understand the underlying mechanism of the treatment effect from acupuncture and, AND assist in building good subsequent prediction models. To this end, taking temporal summation (TS) first as an example, we will first estimate the correlation coefficients between baseline TS and the primary outcome (% pain reduction immediately after treatment) and then perform multivariate linear regression with clinical pain reduction as the continuous dependent variable and TS and potential confounding factors such as the demographic variables and the baseline pain level as independent variables in the verum arm. We will estimate the regression coefficients and their 95% confidence intervals, which will be used to formally test association between TS and pain reduction with or without adjustment of potential confounders. To evaluate the predictiveness of TS (with other patients' characteristics) to pain reduction, we will also calculate the mean squared prediction error of the multivariate regression model. Variable selection method such as lasso may be used to remove unnecessary predictors from the model and cross-validation will be used to estimate the prediction accuracy to account for the adaptive model building step. Likewise, we will repeat the analysis in the sham arm. Specifically, we will test the presence of the association by examining if zero is inside the interval for confirming the hypothesis that the association is close to null in the sham arm. We will also estimate the interaction between the treatment group and TS to determine if decreased TS better predicts treatment response to verum than to sham acupuncture. Note that factors which are equally predictive to the pain reduction in both arm in general do not have interaction with the treatment.

1514 In summary, the primary objective will be to assess the predictiveness of baseline TS to pain reduction;  
1515 and the primary outcome of pain reduction will be the difference in pain between baseline and  

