1516 immediately after treatments. The primary analyses will be the computation of mean-squared  
1517 prediction error from a multivariate regression model, as well as the use of Lasso and cross-validation to  
1518 improve and validate the predictive model with TS. The second objective will be to quantify the  
1519 association between TS and pain reduction immediately after treatments (ie secondary outcome is the  
1520 same as the primary outcome, pain reduction immediately after treatments). The secondary analyses  
1521 will be a) computation of the correlation coefficient between baseline TS and pain reduction and b)  
1522 estimation of the regression coefficient and 95% confidence intervals between baseline TS and pain  
1523 reduction in a multivariate regression model taking TS and other baseline variables into account.

1524 The same analyses will be applied to pressure pain threshold and widespread pain. Realizing that pain  
1525 reduction may not be normally distributed and that the assumed linear regression model may not be  
1526 appropriate, we will repeat the above analysis using a conservative, semi-parametric transformation  
1527 model. We will perform the parallel logistic analysis with dichotomized pain-reduction (responder vs  
1528 non-responder) as the binary dependent variable of interest. We will perform similar analyses for  
1529 widespread pain. Finally, we will repeat the above using pain reduction at 6 months post-treatment as  
1530 our outcome variable.

1531 **Aim 2. Explore the predictive relationship and the association between descending pain modulatory**  
1532 **measures and clinical response to acupuncture.**

1533 **Planned analysis:** the statistical plan for Aim 2 is almost identical to that of Aim 1 except, we replace  
1534 baseline factors of TS, pressure pain threshold and widespread pain, with baseline CPM, pain  
1535 catastrophizing, coping effectiveness and self-efficacy. In summary, the primary objective will be to assess  
1536 the predictiveness of baseline descending pain modulatory factors (CPM, pain catastrophizing, coping  
1537 effectiveness and self-efficacy for pain management) to pain reduction; and the primary outcome of  
1538 pain reduction will be the difference in pain between baseline and immediately after treatments. The  
1539 primary analyses will be the computation of mean-squared prediction error from a multivariate  

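### Section 9.6 makes the prediction error of a joint model the primary analysis for Aims 1 and 2; without a model that omits the factor, this does not by itself show whether the factor predicts pain reduction

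*Protocol*

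**What the plan says.** All of the following is in the Protocol.

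- **Primary objective (section 9.6, Aim 1).** "In summary, the primary objective will be to assess the predictiveness of baseline TS to pain reduction".
- **Primary analyses (section 9.6, Aim 1).** MSPE comes first: "immediately after treatments. The primary analyses will be the computation of mean-squared". A second component, meant to better and check the model that contains TS, is brought in with these words: "prediction error from a multivariate regression model, as well as the use of Lasso and cross-validation to".
- **Content of the model.** The regressors are "TS and potential confounding factors such as the demographic variables and the baseline pain level as independent variables in the verum arm". The purpose of the metric is given as follows: "To evaluate the predictiveness of TS (with other patients' characteristics) to pain reduction, we will also calculate the mean squared prediction error of the multivariate".
- **Other factors.** The same analyses apply to pressure pain threshold and widespread pain. Aim 2 repeats the scheme for conditioned pain modulation, catastrophizing, coping and self-efficacy: "primary analyses will be the computation of mean-squared prediction error from a multivariate", again with lasso and cross-validation.
- **Secondary analyses.** These are the correlation with pain reduction and, from the multivariate model, an item worded "estimation of the regression coefficient and 95% confidence intervals between baseline TS and pain". A treatment-by-TS interaction is also planned, but is not listed among the primary analyses.
- **Power (section 9.2).** The predictive objective is called exploratory. Of the two objectives, prediction and association, the protocol will design the "study to power for the latter objective", which is association.

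For Aims 1 and 2, section 9.6 names no covariates-only model, no intercept-only model, no difference in MSPE and no threshold.

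**The concern.** The MSPE of a joint model measures what all its predictors achieve together. Read alone, it cannot be credited to TS. Baseline pain sharpens the problem because section 9.6 summarises the outcome as the difference between baseline and post-treatment pain, so baseline pain is a component of the outcome and is likely to correlate with it. The model may then predict quite well when TS adds nothing.

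At stake is what the primary result may be taken to mean. A favourable MSPE produced by baseline pain could be read as evidence for TS, or for whichever factor was entered. The analyses that would prevent that reading sit one rank lower, although they are the ones the sample size was chosen for.

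**Working it through.** **1. The plan's own figure.** Section 9.2 gives about 80% power for a within-arm correlation of 0.4 with 50 patients at alpha 0.05, by Fisher's transformation. Taking the test as two-sided (the protocol does not say):

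Power = Φ(atanh(0.4) × √(50 − 3) − 1.96) = Φ(0.4236 × 6.856 − 1.96) = Φ(0.944) = 82.8%.

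This agrees with the stated figure; 80% is first reached at n = 47. The calculation concerns the correlation, which section 9.6 ranks secondary. No precision or power is given for the MSPE.

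**2. How strongly baseline pain might relate to the outcome.** The documents give no figure, so this is an assumption. If pre- and post-treatment pain have equal variances and correlation ρ, the correlation of baseline pain with (baseline − post) is √((1 − ρ)/2):

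- ρ = 0.82 gives 0.3
- ρ = 0.68 gives 0.4
- ρ = 0.50 gives 0.5

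The range 0.3 to 0.5 is used below. Section 9.6 also calls the outcome a percentage reduction, for which the relation may differ.

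**3. Can the full-model MSPE tell a null TS from a real one?** Simulation of one arm: n = 50, outcome variance 1, four covariates independent of TS, least squares, 10-fold cross-validation, 1000 runs per row.

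| Covariate R² | TS correlation | MSPE, full model | MSPE, without TS | Full beats model without TS | Full beats intercept-only |
|---|---|---|---|---|---|
| 0 | 0 | 1.162 | 1.133 | 19% | 9% |
| 0 | 0.4 | 0.966 | 1.132 | 92% | 64% |
| 16% | 0 | 0.966 | 0.943 | 20% | 62% |
| 16% | 0.4 | 0.784 | 0.942 | 94% | 95% |
| 30% | 0 | 0.805 | 0.783 | 18% | 93% |
| 30% | 0.4 | 0.622 | 0.783 | 97% | 99% |

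Rows 2 and 3 are the core of the matter. The full-model MSPE averages 0.966 both when TS has the planning correlation and the covariates explain nothing, and when TS has no effect and the covariates explain 16%. An intercept-only comparison does not separate these two cases (64% against 62%). The model without TS does (92% against 20%).

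**4. With the covariates the protocol describes.** Model of baseline pain, age, sex and TS; n = 50; 1500 runs per scenario. Ranges cover independent repeats. With TS unrelated to outcome:

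| Assumed baseline-pain correlation | Full beats intercept-only | Full beats covariate-only |
|---|---|---|
| 0.3 | roughly 45-48% | about 17-20% |
| 0.4 | 70% | about 17-20% |
| 0.5 | 87-90% | about 17-20% |

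At a baseline-pain correlation of 0.4, the full-model MSPE averages about 0.94, 0.90 and 0.76 for TS correlations of 0, 0.2 and 0.4. It does fall as TS matters more, but the null value cannot be known without fitting the model that omits TS.

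**5. Does lasso fill the gap?** Under the assumptions of step 3 (300 runs), the minimum-error penalty keeps a null TS in 13%, 42% and 62% of runs for covariate R² of 0, 16% and 30%. The one-standard-error rule keeps it in 0.3%, 3% and 10%. With a TS correlation of 0.4 and covariate R² of 16%, the two rules keep TS in 96% and 64% of runs. Retention carries some information about TS, but what it means depends on a rule that section 9.6 does not state.

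**6. Do the planned secondary analyses isolate TS?** In the setting of step 4 with a baseline-pain correlation of 0.4, the adjusted-coefficient test rejects a null TS in about 5-6% of runs and detects a correlation of 0.4 in 88-89%. They do.

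**The case against.** A reader might infer that the trial cannot say whether TS predicts pain reduction. The documents do not support that. The adjusted coefficient comes from a regression that includes baseline pain, and it tests exactly whether TS adds to it. The unadjusted correlation and the interaction with treatment are planned too, and Aim 2 follows an almost identical plan. A good MSPE driven by baseline pain would be reported beside a TS coefficient near zero. This stands, and it limits the point to how the primary analysis is specified and ranked.

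Nor is the primary analysis a single number. Lasso and cross-validation are part of it, and lasso dropping TS would say something about TS. That stands in part: there is a signal, but no criterion for reading it.

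It can also be argued that section 9.6 means joint prediction, since one sentence speaks of TS with other patient characteristics. The summary sentence, however, sets the primary objective as the predictiveness of baseline TS, and the reader has to judge the metric against that.

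Finally, the aims are declared exploratory, verification in larger trials is foreseen, and no success threshold hangs on the MSPE for Aims 1 and 2. This lowers the stakes. It does not turn the matter into detail left to an analysis plan, because the protocol itself names the primary metric and places it above the factor-specific tests.

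**Conclusion.** The point holds in limited form. For every Aim 1 and Aim 2 factor, the designated primary analysis does not by itself answer the designated primary objective, because the factor is never removed from the model for comparison. The analyses that isolate the factor are planned and adequately powered at the planning correlation of 0.4, but ranked secondary. The defect can therefore be repaired from data the trial already collects.

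The logical part needs no assumption: one joint prediction error cannot be apportioned to one predictor. The sizes do rest on assumptions: 50 analysable patients in the arm, covariates independent of TS, and baseline-pain correlations of 0.3 to 0.5 that the documents do not give. At 0.3 the full model with a null TS beats intercept-only in slightly under half of runs, so the risk of a misleadingly good MSPE is moderate there and becomes high only at 0.4 and above. The protocol does not plan an intercept-only comparison for these aims. It is used here only to show what a natural reading of a low MSPE would be worth.

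**What to change.** In section 9.6, for each Aim 1 and Aim 2 factor:

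1. Define the primary predictive quantity as the difference in cross-validated MSPE (or cross-validated R²) between the covariate model with the factor and the same model without it, using the same patients and the same folds.
2. Leave the factor unpenalised if lasso is applied to the covariates, so that the comparison always concerns that factor.
3. Give an interval from a bootstrap that resamples patients and repeats the whole procedure, including any selection step. Repeating the fold split alone reflects only splitting variation and would give too narrow an interval.
4. Interpret the difference together with the planned adjusted coefficient and its 95% CI. The sign of the difference is not a test: a null factor still improves the cross-validated error in about one run in five.

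Alternatively, make the association test that section 9.2 powers the primary analysis and present MSPE as descriptive. This brings sections 9.2 and 9.6 into line without a new metric.

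The first route costs wording, one extra model per factor and computing time for the bootstrap. The second costs wording only. Neither needs new data, visits or patients.

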## **1. STUDY OBJECTIVES**

### **1.1 Primary Objective**

**Aim 1.** Explore the predictive relationship and the association between *ascending sensitization* measures and clinical response to acupuncture.

*Hypothesis 1: augmented temporal summation (TS), and more wide-spread pain (WSP) (quantified by number of painful areas marked by the participant on a standardized body map) will be associated with greater pain reduction in the verum arm than in the placebo arm; decreased pressure pain threshold (PPTr) will be associated with greater pain reduction in the placebo arm than the verum arm.*

*Aim 2. Explore the predictive relationship and the association between **descending modulatory** measures and clinical response to acupuncture.*

*Hypothesis 2: decreased conditioned pain modulation (CPM), and more favorable psychological state, measured by less pain catastrophizing, better self-efficacy in coping and in pain management, will be associated with greater pain reduction in the verum than the placebo arm; expectation of positive treatment outcome will be associated with pain reduction in both the verum and the placebo arm.*

*Aim 3. **Exploratory model building** to predict pain reduction by electroacupuncture.*

*Hypothesis 3. A mathematical model relating key baseline characteristics to percent pain reduction will be developed using advanced techniques, and this model will be tested using cross-validation within the proposed pilot.*

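### The predictor-by-arm interaction is planned and powered, but the section 9.6 summaries give it no rank, although only this contrast tests the between-arm hypotheses

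*Protocol*

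**What the plan says.** **Hypotheses (protocol 1.1, repeated in 9.1).** Hypothesis 1 links augmented temporal summation (TS) and widespread pain to "greater pain reduction in the verum arm than in the placebo arm"; for a low pressure pain threshold the direction favours placebo. Hypothesis 2 makes the same kind of verum-over-placebo statement for conditioned pain modulation, catastrophizing and self-efficacy. Only expectation is predicted to matter in both arms.

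**Power (9.2).** Of the prediction and association objectives, prediction is set aside: "because the former is exploratory in nature, we will design our" study around the association. The claim is "With 50 patients per arm, we will be able" "to detect a moderate correlation of 0.4" "with approximately 80% power with alpha of 0.05 using Fisher's transformation". The interaction is then to be tested, with 80% power claimed for a difference of 0.5 between the two arms' correlations.

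**Analysis (9.6, Aim 1, before the summary).** Correlation and regression are run in the verum arm and repeated in the sham arm. There, a confidence interval that contains zero is to confirm that the association is close to null. The team will also "estimate the interaction between the treatment group and TS". The paragraph closes by noting that factors equally predictive in both arms generally show no interaction.

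**Ranking (9.6 summaries).** "In summary, the primary objective will be to assess the predictiveness of baseline TS to pain reduction". The primary analyses are mean-squared prediction error, lasso and cross-validation. The secondary analyses "will be a) computation of the correlation coefficient between baseline TS and pain reduction and b", item b being the adjusted regression coefficient with its 95% CI. The Aim 2 summary has the same structure. Neither summary names the interaction.

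**The concern.** Three contrasts are in play: prediction error, the association within an arm, and the interaction. They answer different questions. A factor tied to natural course, regression to the mean or placebo response can correlate with improvement among verum patients and lower prediction error there, yet say nothing about who gains more from verum than from sham. Only the interaction, which compares the randomised arms directly, separates the two.

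The summaries rank the first two contrasts and not the third. Section 9.2 puts association ahead of prediction, and section 9.6 reverses that order. Someone reporting the trial could therefore defend any of the three as the result that settles Hypothesis 1. The sham-arm step adds to the problem because it invites a comparison of significance across arms (present in verum, absent in sham) in place of a test of the difference.

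**Working it through.** **Inputs.** From protocol 9.2: 50 per arm, within-arm correlation 0.4, correlation difference 0.5, alpha 0.05, Fisher's transformation. Assumed: two-sided tests (sidedness is not stated) and complete data on all 50 per arm.

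**Formulas.** Φ is the normal distribution function, and √(50 − 3) = 6.856.
- Within one arm: d = atanh(r) × √(n − 3); power = Φ(d − 1.96) + Φ(−d − 1.96).
- Between arms: d = |atanh(r₁) − atanh(r₂)| / √(2/(n − 3)), same power formula; √(2/47) = 0.2063.

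**Step 1: the plan's own figures.**
- Within verum, r = 0.4: d = 0.4236 × 6.856 = 2.904, power 82.8%. This agrees with the stated figure of about 80%.
- Interaction, difference 0.5: the answer depends on which pair is meant, and section 9.2 does not say. Two-sided power is 82.0% for 0.6 versus 0.1, 75.9% for 0.5 versus 0, 71.9% for 0.4 versus −0.1 and 69.7% for 0.25 versus −0.25. One-sided, the last two become 81.5% and 79.7%. The stated 80% is reachable, but not for every pair.

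**Step 2: a purely prognostic factor.** Assume the same true correlation r in both arms, so that the between-arm hypothesis is false. With p the power within one arm and the arms independent, the chance of significance in verum but not in sham is p(1 − p).

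| r in both arms | Verum test significant (p) | Sham test not significant (1 − p) | Verum significant, sham not | Interaction significant |
|---|---|---|---|---|
| 0.4 | 83% | 17% | 0.828 × 0.172 = 14% | 5% |
| 0.3 | 56% | 44% | 0.564 × 0.436 = 25% | 5% |
| 0.2 | 28% | 72% | 0.285 × 0.715 = 20% | 5% |

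The last column is the nominal size, because the true difference is zero.

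**Step 3: what a sham interval containing zero can show.** On the correlation scale, an observed sham correlation of exactly zero has 95% limits of ±tanh(1.96/6.856) = ±0.28. Even the most null-looking result leaves correlations up to 0.28 in either direction open. The third column of the table says the same: a true sham correlation of 0.3 would give an interval containing zero in 44% of trials.

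**Step 4: the price of relying on the interaction.** For 0.4 in verum and 0 in sham: d = 0.4236/0.2063 = 2.054, power about 54%. For 80% power, n per arm = 2 × [(1.960 + 0.842)/0.4236]² + 3 = 90.5, that is 91.

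**Step 5: the passages side by side.**

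| Contrast | Section 9.2 | Section 9.6 body | Section 9.6 summaries |
|---|---|---|---|
| Prediction error | exploratory, not powered | first goal | primary |
| Within-arm association | powered first | second goal | secondary |
| Interaction | powered next | to be estimated | not listed |

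**The case against.** The strongest reply is that nothing is missing. Section 9.2 says the interaction will be tested for exactly this purpose and gives it a power statement. Section 9.6 plans it for TS, applies the same analyses to pressure pain threshold and widespread pain, and calls the Aim 2 plan nearly identical. The authors draw the distinction between prognostic and predictive factors themselves. The summaries follow the wording of the Aims, which are to explore prediction and association. The aims are called exploratory, and confirmation is left to larger trials. Most of this stands.

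A reader might go further and infer that the interaction test has been left out, or that the plan would accept a verum-arm correlation as proof of a verum-over-sham effect. The documents support neither. No passage says that a verum-arm result alone confirms a between-arm hypothesis. The one explicit success criterion, under Aim 3, compares verum with sham in a selected subgroup. It would also be wrong to read 83%, 56% and 28% as false-positive rates of the plan. They are the power to detect a real verum-arm association, and they become errors only under a decision rule that the plan does not state.

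The reply does not remove the inconsistency. The protocol chose to rank its analyses, ranked them differently in two sections, and gave no status to the contrast that tests its hypotheses. An analysis plan not shown here might settle this, but the conflict lies within the protocol. The exploratory label does not help either: a multiplicity correction cannot turn a real prognostic association into evidence about verum over sham.

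**Conclusion.** The point holds as a defect of status and consistency, not as a missing test. The interaction is planned and powered, but it is unranked in the summaries for Aims 1 and 2. Sections 9.2 and 9.6 order prediction and association differently. The sham-arm confirmation step asks more of 50 patients than they can give.

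The size is illustrative. If a factor has the same correlation in both arms, reading the arms separately gives significance in verum but not in sham in 14% to 25% of trials for r between 0.2 and 0.4, against 5% for the interaction. This rests on that equal-correlation assumption, two-sided 0.05, 50 analysed per arm and the Fisher approximation. The change is worth making because it is cheap and limits what can be claimed. Demoting the prediction objective is not required.

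**What to change.** - In the section 9.6 summaries for Aims 1 and 2, name the predictor-by-arm interaction coefficient with its 95% CI as the analysis that decides each between-arm hypothesis. Estimate it in one model with both arms, adjusted for baseline pain.
- State that a factor is claimed to predict response to verum over sham only on that contrast.
- Present within-arm correlations and slopes as descriptive for that question.
- Delete the step that takes a sham-arm interval containing zero as confirming a null association; report the estimate and its interval.
- Make the ranking in sections 9.2 and 9.6 agree. Prediction error and lasso can stay as a separate prediction aim.
- While editing the interaction sentence in section 9.6, reconcile its direction with Hypothesis 1: it speaks of decreased TS, the hypothesis of augmented TS.

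The cost is rewording in two sections, with no new data and no change to the planned 100 participants. The real downside is power: about 54% at 50 per arm if the correlations are 0.4 and 0, against about 83% for the verum-only test. The protocol should say so, so that a wide interaction interval is read as inconclusive.
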